### Design and setting of the study

This project is a quasi-experimental pre-test post-test intervention with a control group [19] using quantitative as well as qualitative methods.

### Participants

The inclusion criteria are men and women between 20 and 67 years, diagnosed with the stress related ICD-10 diagnoses F43.8 and F43.9 [20], and with contact in primary care due to their symptoms of stress. Exclusion criteria are severe somatic disorders, neuropsychiatric diagnosis, psychosis and language or cognitive problems that implies difficulties in completing questionnaires.

### Context and procedure

The project takes place within the primary healthcare services in two regions in southern Sweden. Five primary care centres recruit participants to the intervention group while five others recruit participants to the control group. Primary care centres who have shown interest in the project have been engaged, and the units themselves chose whether to participate as part of the intervention group or the control group. The primary care centres, however, are comparable in terms of the size of cities where they are situated, socio-economic conditions, and provision of treatment methods. Both groups of participants receive their care as usual in the primary care context.

Potential participants who meet the criteria receive information about the project from a rehabilitation coordinator. When a patient declines to participate, the rehabilitation coordinator informs the project leader about their sex, age, diagnosis, and when possible the reason for declining. This is carried out with the aim of facilitating the exploration of potential differences between those who choose to participate and those who choose not to. When a patient is interested in participating, the rehabilitation coordinator forwards their contact information to the project leader and one of the researchers/project assistants contacts them for a meeting where they receive further information and can ask questions about the study and what participation entails. When agreeing to participate, the patients sign an informed consent and baseline data is collected.

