#### Education prior to the intervention delivery

Five therapists, all of who are occupational therapists (OT), conduct the intervention Be-Well™, i.e. photo-supported conversations about well-being. Prior to commencing the intervention, they have participated in a course lasting two days, including discussions about the method and its background. There was a two-week interval between the first and second days and the education was performed by the research group ([name], PW, [name], UH). The OTs received information about the previous pilot project and its results during the course. The topics of health and well-being [21–24] well-being despite stress-related illness [13, 14], balance in activities in everyday life [25] and visual methodology [15] were also addressed and discussed. Moreover, the topic of photography and pictures was presented together with related ethical issues by a researcher ([name]) with knowledge in the field of visual studies, who also gave a lecture on photo interpretation. The training also involved practical exercises where the OTs tried the method of photographing well-being and talking about their own well-being with each other, based on their photographs, and acting both as a patient and as the therapist.

The OTs also took new pictures about their well-being between the first and the second day and had new conversations about these. Their experiences from these were then focused on in group discussions and reflected upon on several occasions. The intervention and its different sessions were described and discussed in detail so that all therapists had good knowledge of it at the end of the two-day course. The OTs discussed with each other and with the researchers throughout the course, and at the end of the second day, they had further opportunities to get answers to any remaining questions and solutions for any issues that were outstanding.

The project leader has continuous contact with the OTs to discuss their progress and clarify potential issues after the education and throughout the project. The OTs also meet regularly to discuss together with the researchers and the project assistants.

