### Sample size

The power calculation for this study was based on the Karolinska Exhaustion Disorder Scale (KEDS) [26]. In a previous study where this instrument was used, the response within each subject group was normally distributed with standard deviation 8.74 [43]. It was thus anticipated that if the true difference in KEDS means (scale on 0–54) between the experimental and control is 7, we will need to study 29 experimental subjects and 29 control subjects to be able to reject the null hypothesis that the population means of the experimental and control groups are equal with probability (power) 0.8. As this study has several timepoints, it is likely that there will be dropouts from the study, and we will thus include a total of 35 experimental subjects and 35 control subjects. The Type I error probability associated with this test of this null hypothesis is 0.05.

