### Analysis

Non-parametric statistics will be used for investigating potential differences between the intervention and control groups in health, and activity-related variables as well as in client satisfaction since the instruments are based on nominal and ordinal scales. Missing data for dropouts will be estimated using the last data obtained before a participant dropped out. The transcribed interviews will be analysed for meanings using thematic [44] and phenomenological [42] analysis. The qualitative data will be analysed for meanings in accordance with the methodological principles of openness, flexibility and a reflective attitude. The analysis is a process defined by a movement between the whole and the parts, with the purpose of identifying a new whole in the phenomenological studies [42] and identifying themes of meanings in the thematic studies [44]. The photographs will be analysed with a semiotic method [45] regarding content and formal aspects, such as shape and color, perspective, spatiality and composition.

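### Arm is fixed by primary care centre (5 versus 5), but the sample size treats patients as independent, so power 0.8 and Type I error 0.05 are not jointly supported for this 10-centre design

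*Protocol article*

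**What the plan says.** **Allocation** (Context and procedure): "Five primary care centres recruit participants to the intervention group while five others recruit participants to the control group". The same section says that the centres chose their own arm, so centre determines arm completely.

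**Delivery** (Education prior to the intervention delivery): "Five therapists, all of who are occupational therapists (OT), conduct the intervention". The article does not say how these therapists are distributed over the five intervention centres.

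**Sample size**: the calculation is for a test to "reject the null hypothesis that the population means of the experimental and control groups are equal". It assumes a 7-point difference on KEDS and a standard deviation of 8.74: "we will need to study 29 experimental subjects and 29 control subjects to be able to reject the null hypothesis", with power 0.8. "The Type I error probability associated with this test of this null hypothesis is 0.05". The increase to 35 per arm is attributed to dropout. Centre, ICC and design effect do not appear.

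**Analysis**: "Non-parametric statistics will be used for investigating potential differences between the intervention and control groups". The reason given is the nominal and ordinal scaling of the instruments. No test is named, and no centre or therapist term is mentioned. Dropouts are handled by carrying the last value forward, so up to 35 per arm may enter the analysis.

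**The concern.** Patients of one centre share staff, referral habits, local care as usual and catchment population, so their KEDS scores are likely to be somewhat alike. When a whole centre belongs to one arm, that likeness does not cancel between arms. It adds to the variance of the difference between arms. A calculation that counts 58 or 70 independent patients leaves this out.

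There are two possible consequences, and they belong to different analyses:

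- If the analysis ignores centre, the standard error is too small and the true Type I error exceeds 0.05.
- If the analysis respects centre, 0.05 is kept but power is lower, because the effective sample is smaller and only 10 units carry the comparison.

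In neither case do 0.8 and 0.05 hold together as the article claims. At stake is the p-value and confidence interval for the primary outcome, which is the main quantitative result of the study.

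**Working it through.** **Inputs from the article.** Difference 7; SD 8.74; Type I error 0.05; power 0.8; 29 per arm evaluable and 35 recruited; 5 centres per arm. Mean centre size is m = 29/5 = 5.8 or 35/5 = 7.

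**Assumed, because the article does not give them.** A two-sided test (the null hypothesis is equality of means); ICC 0.02 / 0.05 / 0.10, with 0 and 0.01 for reference; equal centre sizes; baseline-to-outcome correlation r = 0.5 where adjustment is considered.

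**1. The plan's own figure.** Under independence, n per arm = 2(1.96 + 0.8416)² × 8.74² / 7² = 24.5, so 25. The exact t calculation gives 26 (power 0.808). At 29 per arm the power is 0.85 (t test), or 0.83 for a simulated Mann-Whitney test. The stated 29 is thus slightly conservative. An unstated allowance for a rank test could explain it (26/0.955 = 27.2, so 28; or 24.5/0.864 = 28.3, so 29), and it is not treated as an error here. The step to 35 follows from dropout alone: 29/(1 − 6/35) = 35. Nothing in the stated calculation is labelled an allowance for clustering.

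**2. Design effect.** DE = 1 + (m − 1) × ICC.

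| ICC | DE, 29 per arm | DE, 35 per arm |
|---|---|---|
| 0.01 | 1.05 | 1.06 |
| 0.02 | 1.10 | 1.12 |
| 0.05 | 1.24 | 1.30 |
| 0.10 | 1.48 | 1.60 |

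**3. Type I error if centre is ignored.** Approximation: 2 × [1 − Φ(1.96/√DE)]. The simulation used 20,000 Mann-Whitney tests per cell, with 5 centres per arm.

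| ICC | 29: formula | 29: simulated | 35: formula | 35: simulated |
|---|---|---|---|---|
| 0 | 0.050 | 0.046 | 0.050 | 0.049 |
| 0.01 | 0.056 | 0.054 | 0.057 | 0.052 |
| 0.02 | 0.061 | 0.057 | 0.064 | 0.059 |
| 0.05 | 0.078 | 0.077 | 0.086 | 0.085 |
| 0.10 | 0.107 | 0.099 | 0.121 | 0.116 |

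At 35 per arm this is about 6% / 8% / 12% for ICC 0.02 / 0.05 / 0.10. The same unadjusted test still rejects often when the 7-point difference is real (0.81 at ICC 0.05, 29 per arm). Its fault is the Type I error, not low power.

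**4. Power if centre is respected.** SE = 8.74 × √(2 × DE × (1 − r²)/n), non-centrality = 7/SE, t distribution with 10 − 2 = 8 df, critical value 2.306. Example with n = 29, ICC 0.05, r = 0: SE = 8.74 × √(2 × 1.24/29) = 2.556, non-centrality 2.739, power 0.67.

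| ICC | 29, r = 0 | 35, r = 0 | 29, r = 0.5 | 35, r = 0.5 |
|---|---|---|---|---|
| 0 | 0.76 | 0.83 | 0.87 | 0.92 |
| 0.02 | 0.72 | 0.79 | 0.84 | 0.89 |
| 0.05 | 0.67 | 0.73 | 0.79 | 0.84 |
| 0.10 | 0.60 | 0.64 | 0.72 | 0.76 |

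The r = 0.5 columns apply the same variance reduction to the between-centre and within-centre parts and keep 8 df, so they are approximate.

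**5. How far the spare power reaches.** With the plain design effect and a normal approximation, power stays at 0.8 while n/DE is at least 24.47. This gives ICC ≤ (29/24.47 − 1)/4.8 = 0.039 at 29 per arm and ICC ≤ (35/24.47 − 1)/6 = 0.072 at 35. This calculation ignores the loss from having only 8 df.

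**The case against.** The strongest reply has four parts.

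- **The article is condensed and its analysis sentence names no test.** Stratified, cluster-level and permutation methods are all non-parametric. A reader might infer that the planned analysis definitely ignores centre. The text does not support that: it is silent, and a fuller plan may specify a centre-respecting method. This stands, and the Type I error figures apply only if centre is ignored. It does not rescue the Sample size section, which sets out its inputs and its reason for inflation and makes a definite claim for independent patients.
- **The size depends on an ICC that nobody has stated.** This stands. At 0.01 to 0.02 the excess Type I error is about one percentage point or less. The 8% to 12% figures need 0.05 to 0.10.
- **Much of the power loss is not clustering.** This also stands. At ICC 0 the 8-df test already has power 0.76 at 29 per arm. The stated inputs need only about 26 per arm, so there is some reserve, and baseline adjustment could recover most of the loss.
- **Therapist effects are not established.** A reader might infer that each therapist serves one centre and that therapist clustering can be quantified. The article does not say so, and the figures above model centre only.

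It is also tempting to say that inflated Type I error and lost power both afflict the same analysis. They do not; each belongs to one of the two ways of analysing the data. The article's remark that the centres are comparable in city size, socio-economic conditions and treatment provision addresses bias between arms, not correlation within centres.

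**Conclusion.** The point holds for the published design claim. Arm is a centre-level factor with five centres on each side, and the stated pair of 0.8 and 0.05 was derived for independent patients. For any positive ICC, a test that ignores centre exceeds 0.05. A centre-level test at 29 per arm without baseline adjustment falls short of 0.8 even at ICC 0. At 35 per arm it is just below 0.8 at ICC 0.02 (0.79) and clearly below it at 0.05 and 0.10.

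The direction is certain given a positive ICC. The size is not, because it rests on an assumed ICC of 0.02 to 0.10, equal centre sizes and, for the adjusted figures, r = 0.5. At the low end of the range the problem is modest. With baseline adjustment and all 35 per arm analysed, power would be 0.89 / 0.84 / 0.76, so the trial may well remain adequately powered once the analysis is properly specified. What the documents support is a claim stated for the wrong unit, not a conclusion that the trial cannot answer its question.

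**What to change.** 1. **Analysis.** State that the primary KEDS comparison respects centre and adjusts for baseline KEDS, which is already collected. Two routes are suitable:
   - a baseline-adjusted centre-level comparison, by a t test on about 8 df or a 5-versus-5 permutation test. The permutation test keeps the non-parametric rationale. It has 10!/(5! × 5!) = 252 arrangements, so its smallest two-sided p-value is 2/252 = 0.008. As centres were not randomised, it relies on centres being exchangeable under the null hypothesis;
   - a mixed model with a random centre intercept and Kenward-Roger or Satterthwaite degrees of freedom. This treats the KEDS sum as continuous, so the ordinal-scale argument in the Analysis section would need a sentence of justification.
2. **Power.** Keep 70 patients and restate the power for 10 centres over a stated ICC range and baseline correlation.
3. **Reporting.** Give the observed ICC and the number of patients per centre and per therapist.

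The cost is some rewording, wider intervals and a less favourable power figure. No patients, centres or assessments are added. Two things remain unsolved and should be stated as limitations: confounding from centres choosing their arm, and the inability to separate therapist from centre effects on the information given.

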#### Education prior to the intervention delivery

Five therapists, all of who are occupational therapists (OT), conduct the intervention Be-Well™, i.e. photo-supported conversations about well-being. Prior to commencing the intervention, they have participated in a course lasting two days, including discussions about the method and its background. There was a two-week interval between the first and second days and the education was performed by the research group ([name], PW, [name], UH). The OTs received information about the previous pilot project and its results during the course. The topics of health and well-being [21–24] well-being despite stress-related illness [13, 14], balance in activities in everyday life [25] and visual methodology [15] were also addressed and discussed. Moreover, the topic of photography and pictures was presented together with related ethical issues by a researcher ([name]) with knowledge in the field of visual studies, who also gave a lecture on photo interpretation. The training also involved practical exercises where the OTs tried the method of photographing well-being and talking about their own well-being with each other, based on their photographs, and acting both as a patient and as the therapist.

The OTs also took new pictures about their well-being between the first and the second day and had new conversations about these. Their experiences from these were then focused on in group discussions and reflected upon on several occasions. The intervention and its different sessions were described and discussed in detail so that all therapists had good knowledge of it at the end of the two-day course. The OTs discussed with each other and with the researchers throughout the course, and at the end of the second day, they had further opportunities to get answers to any remaining questions and solutions for any issues that were outstanding.

The project leader has continuous contact with the OTs to discuss their progress and clarify potential issues after the education and throughout the project. The OTs also meet regularly to discuss together with the researchers and the project assistants.

### The intervention

The intervention group received photo-supported conversations about well-being, i.e. the intervention Be-Well™, in addition to care as usual. The intervention has been developed on the basis of previous studies in the pilot project [13, 14], and on knowledge about health, well-being and everyday life activities [23, 24], and visual methodology [15].

The intervention is individually conducted, and the patients meet their occupational therapist (OT) physically and/or virtually for 12 sessions (intended to be conducted within 12 to 15 weeks). The intervention consists of three parts, sessions 1–4, sessions 5–10 and, sessions 11–12.

Sessions 1 to 4 are full-length 60-min meetings with the therapist. They were originally intended to be physical meetings but due to the Covid-19 pandemic they can also be switched to be virtual. The patient takes photographs of what they see as being related to their well-being prior to each of the sessions and sends 1–3 of these photographs to the OT before the session. The OT enlarges each of the photographs to the A4 size and brings them to the session. The conversation during the session is based on the photographs and the patient is encouraged to talk about each of them and how they relate to their well-being as well as the feelings or thoughts related to the photograph. Potential strategies for everyday life are discussed, e.g. to do more or less of an activity which relates to their well-being or solve a difficult activity in another way, and these strategies are tested between the sessions. Sessions 2 to 4 begin with a reflection on the last session before the new photographs are discussed.

Sessions 5–10 are short virtual meetings of approximately 15–20 min with the aim of following the patient, confirming their process and supporting them in their direction towards increased well-being. The patient continues photographing well-being, discusses these photographs shortly with their OT as well as their self-given homework to increase their well-being.

The final two sessions are 60-min physical or virtual meetings where the aim is to compile the patient’s experiences of well-being together with the previous sessions and to formulate their continued activity. The patient is encouraged to “look in the rear-view mirror” during session 11 by viewing and reflecting upon all their previous photographs, which are placed in front of them. The intention is to look forward by reflecting upon their photographs during session 12. The patient is asked what he/she wants to take away from the intervention as well as being recommended to give themselves advice about how to keep or find situations in their everyday life that are of importance for their well-being. The patient is also asked to choose one or two of their enlarged pictures to use as a reminder of everyday life or as a future goal.

### Control

The control group receives their care as usual, e.g. medication, physiotherapy, psychotherapy, occupational therapy and/or vocational interventions. The therapists who recruit patients (nurses, OTs, psychologists and social workers), also meet regularly to discuss the recruiting with the researchers and project assistants.

### Data collection

Two researchers ([name], UH), and one project assistant collect the data for the intervention group and three project assistants collect data for the control group. The project assistants are OTs, who are not involved in the intervention. All project assistants have been informed about the project and its aim and the project leader will have continuous contact with them throughout the project to discuss progress and clarify potential issues. The project assistants also meet regularly to discuss together with the researchers and the therapists.

The intervention group meets the data collector prior to the start of the intervention; after the intervention; and 6 months after the performed intervention ended. The control group meets the data collector at the same time points as the intervention group (Fig. 1). In order to protect their confidentiality, all the participants received a code number when recruited, and the list linking names to code numbers is stored separately.

**Fig. 1 Fig1:**
[figure not shown]
Overview of the procedure

#### Data material

The data in this project consists of questionnaires, interviews and photographs.

#### Quantitative measures

Participants in the intervention and in the control group answer the same questions including gender, age, diagnosis, social network, employment, sick leave/not sick leave, work situation and degree of paid work, physical activities, and care consumption. As the project takes place during the pandemic Covid-19, the participants are also asked about whether and how they are affected by the pandemic in their personal lives, as well as in relation to their paid work.

##### Primary outcomes

*Health related aspects* are measured in terms of; *Symptoms of exhaustion,* using the Karolinska Exhaustion Disorder Scale (KEDS) [26]. The instrument has nine items measuring symptoms of exhaustion, cognitive problems, sleeping, and tolerance to further stress on a seven-step ordinal scale from 0 to 6 where higher is worse and is summed with a cut-off of 19. The instrument originates from Sweden and has shown good psychometric properties [26].

##### Secondary outcomes

*Health and well-being related aspects* are measured in terms of; *Symptoms of depression and anxiety, quality of life, sense of coherence, and client satisfaction. Depression and anxiety* is measured with the Hospital Anxiety and Depression Scale (HADS) [27]. It consists of seven items measuring symptoms of depression and anxiety respectively, and can be measured as a whole, or forming two sub-scales. Each item is measured on a four-step ordinal scale from 0 to 3 where higher is worse. The Swedish version of the instrument is commonly used and found appropriate [28, 29].

*Quality of life* is measured by using the Manchester Short Assessment of quality of life (MANSA) [30]. The instrument is interview-based and has twelve items that measure satisfaction with life, and aspects of life as accommodation, work, leisure, relationships, accommodation, and physical and mental health on a seven step ordinal scale from 1 to 7 where higher is better and can be summed. The Swedish version of the instrument has previously shown good psychometric properties [31].

*Sense of coherence* is measured with the Sense of Coherence Scale (SoC) [32]. The 13 items scale measures how well individuals are coping with life stress and psychological stress on seven-steps ordinal scales from 1 to 7, higher is better and it can be summed. The Swedish version of the instrument is frequently used and has shown good psychometric properties [33].

*Activity related aspects* are measured in terms of: balance of activities in everyday life and work ability. *Balance of activities in everyday life* is measured by using the Occupational Balance Questionnaire (OBQ11) [34], which focuses on satisfaction with the amount and variation of occupations in everyday life. The OBQ11consists of eleven items measured on a four-step ordinal scale from 0 to 3 where higher is better and can be analysed on item level and as a summed scale. The instrument originates from Sweden and has shown good psychometric properties [34, 35].

*Work ability* is measured with the Worker Role Self-assessment (WRS-18) [36]. This instrument measures self-rated perceptions of current and future work and work role. The instrument has 18 items measured on five-step ordinal scales from 1 to 5 where higher is better. The instrument originates from Sweden and has shown good psychometric properties [37].

*Client satisfaction* is measured with the Client Satisfaction Questionnaire (CSQ) [38]. The instrument has eight items and measures satisfaction with received treatment on a four-step ordinal scale from 1 to 4 where higher is better. It has previously been found to have good psychometric properties [39, 40] in a Swedish context [41].

